### Patient selection: Exclusion criteria

Patients presenting with any of the following criteria will not be included in the trial:

- refusal of the patients to take part in the study

- previous radiotherapy of the hepatobiliary system

- margin of < 1 cm between tumor edge and intestines

- Patients who have not yet recovered from acute toxicities of prior therapies

- Known carcinoma < 2 years ago (excluding Carcinoma in situ of the cervix, basal cell carcinoma, squamous cell carcinoma of the skin) requiring immediate treatment interfering with study therapy

- Pregnant or lactating women

- Participation in another clinical study or observation period of competing trials, respectively

### Treatment Planning

For particle therapy, patients will be immobilized using an individually manufactured body fixation or positioning device including abdominal pressure plates as described in detail previously [26]. For treatment planning, contrast-enhanced CT (3 mm slice thickness) as well as MR-imaging will be performed for optimal target definition. 4D-CT-imaging is considered standard of care for target definition and for position verification during the course of radiotherapy when treating patients with moving organs. Interstitial fiducial markers are standard of care for treatment planning and patient positioning during treatment and may be implanted prior to radiotherapy within clinical routine.

Organs at risk such as the intestines, stomach, lungs, kidney, spleen and spinal will be contoured. Dose constraints of normal tissue will be respected according to Emami et al. [41].

The Gross Tumor Volume (GTV) will be defined as the area of solid macroscopic tumor contrast enhancement on CT and MR-imaging. The Clinical Target Volume (CTV) will be defined as the GTV plus a margin of 5 mm. The Planning Target Volume (PTV) will include the CTV plus a margin of about 1 cm to account for residual organ motion and setup inaccuracies.

Carbon ion RT planning is performed using the treatment planning software PT-Planning (Siemens, Erlangen, Germany) including biologic plan optimization. Biologically effective dose distributions will be calculated using the α/ß ratio for HCC as well as for the endpoint late toxicity.

No interruptions > 4 days between during study treatment are allowed.

Patient positioning directly prior to particle therapy will be evaluated by comparison of x-rays for static images as well as fluoroscopic imaging to determine residual organ motion in comparison to the DRRs. Set up deviations > 3 mm are corrected prior to radiotherapy.

### Dose Prescription Carbon Ion Radiotherapy

The intensity-controlled rasterscanning system will be used for beam application.

Within this dose escalation study, total doses and fractions will be applied according to the dosing scheme shown in Table 1.

Treatment planning aims in the coverage of the PTV by the 90%-isodose line.

Dose specification is based on biologic equivalent dose because of the high relative biologic effectiveness (RBE) of carbon ions, which differs throughout the target volume due to its dependence on various factors. RBE will be calculated at each voxel throughout the target volumes and biological optimization will be performed.

### Trial Duration, Schedule and Follow-up

The primary endpoint is acute toxicity of carbon ion radiotherapy observed within 30 days of study treatment.

Patients are scheduled for follow-up visits every 4 weeks after completion of carbon ion radiotherapy for the first 3 months, thereafter in 2-months intervals or as needed clinically including contrast-enhanced MRI as well as thorough clinical-neurological and haematological assessment. These follow-up visits are in line with standard care outside of clinical trials.

The last patient included into the study will be followed for at least 3 months after study treatment. This is considered the final study visit. All other patients will be followed regularly as described in detail until death or until 3 months after LPI.

The overall duration of the trial is expected to be approximately 24 months.

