#### Primary Objective

The primary objective is toxicity of carbon ion radiotherapy and the definition of a MTD for subsequent clinical investigation of carbon ion radiotherapy.

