### Statistical calculations for trial sample size

#### Study hypothesis

The study is designed to demonstrate that carbon ion radiotherapy is safe for the treatment of HCC. The aim of the study is to evaluate the optimal dose tolerated with respect to toxicity.

Unacceptable toxicity (DLT) is defined as any irreversible grade 4 toxicity during a time frame of 30 days as classified by CTCAE version 4.0.

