### Statistical Methods

#### Sample Size Calculation

The calculation of sample size for the PROMETHEUS-01 trial is based on the traditional dose escalation scheme. DLT are considered any irreversible Grade 4 toxicity classified by CTCAE version 4.0 after study treatment.

Patients are treated in cohorts of three each receiving the same dose.

For observation of DLT, patients are observed for 30 days after study treatment. If the last patient of the cohort is observed 30 days after study treatment, patients of the next cohort may be recruited.

If none of the three patients shows a DLT, the next cohort of three patients receives the next higher dose as described above.

Otherwise, if at least one patient of the cohort develops a DLT (1/3), a second cohort of three patients is treated at the same dose level without escalating the dose.

If exactly one out of the six patients (1/6) treated exhibits DLT, the trial continues as planned at the next higher dose level.

If two or more patients out of the six exhibit a DLT, the dose escalation stops at that level and the next lower level is considered as the MTD. When the escalation has stopped, additional patients will be treated at the MTD to a total of nine patients.

This trial is conducted to choose the MTD of carbon ion radiotherapy between five dose levels. Therefore the sample size at maximum is 33 patients (4 dose levels with at maximum 6 patients and 9 patients at the MTD).

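### The MTD rests on 30-day toxicity only, under DLT definitions that disagree on irreversibility; no stated rule lets toxicity from the planned later visits affect escalation or the declared MTD

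*Protocol article*

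**What the plan says.** The primary objective includes "the definition of a MTD for subsequent clinical investigation of carbon ion radiotherapy". Under Trial Duration, Schedule and Follow-up, the endpoint behind it is limited in time: "The primary endpoint is acute toxicity of carbon ion radiotherapy observed within 30 days of study treatment".

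The DLT is defined in four places:

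- Study hypothesis: "Unacceptable toxicity (DLT) is defined as any irreversible grade 4 toxicity during a time frame of 30 days as classified by CTCAE version 4.0".
- Sample Size Calculation: "DLT are considered any irreversible Grade 4 toxicity classified by CTCAE version 4.0 after study treatment". The window follows: "For observation of DLT, patients are observed for 30 days after study treatment".
- Analysis Variables: grade 4, at least possibly related, within 30 days after completion. The qualifier is garbled and runs unpredictable and irreversible together.
- Descriptive Analysis: any grade 4 event at least possibly related, within 30 days after completion, with no irreversibility condition.

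The release rule is: "If the last patient of the cohort is observed 30 days after study treatment, patients of the next cohort may be recruited". Confirmatory Analysis says that the MTD is determined by the traditional scheme and names no other input.

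Follow-up runs longer. Visits are every 4 weeks for 3 months and then every 2 months. "The last patient included into the study will be followed for at least 3 months after study treatment"; the other patients are followed until death or until 3 months after the last patient is included. Safety data are a secondary endpoint and are tabulated by dose level.

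**The concern.** Two features of the rule can only lower the DLT count.

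First, a related grade 4 event after day 30 has no stated route into the dose decision, even when it is on file before a higher level opens.

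Second, where irreversibility is required, nothing says when it is judged or how an event still unresolved at day 30 is scored. The same event can be a DLT under one section and not under another, so two people applying the text could reach different escalation decisions.

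At stake is the MTD that later trials will take over. If a material share of serious toxicity appears after day 30, that dose will tend to be set too high relative to the toxicity the trial itself records.

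**Working it through.** **1. The plan's own figure.** Maximum sample size: 4 levels × 6 + 9 at the MTD = 33. This reproduces. The window changes which events count, not cohort sizes, so 33 is unaffected.

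**2. Can irreversibility be shown in the window?** With visits every 4 weeks, the one regular post-treatment visit inside the window falls at about day 28. An event first found there leaves 30 − 28 = 2 days before the next cohort may open. An event starting on day 25 leaves 30 − 25 = 5 days.

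**3. What is on file but unused?** Take the shortest case: one cohort per level, with no recruitment or treatment time. When level 5 opens, patients at levels 1 to 4 have at least 120, 90, 60 and 30 days of follow-up. When level 5 is itself judged, they have 150, 120, 90 and 60. The rule reads 30 days for each. A related grade 4 event on day 45 at level 3 would be known before level 5 opened, and the rule would not use it.

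**4. Effect on escalation.** Under Sample Size Calculation, a level is passed with 0/3 DLTs, or with 1/3 followed by 0/3. With p the DLT probability visible by day 30:

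P(escalate) = (1 − p)³ + 3p(1 − p)²(1 − p)³ = (1 − p)³ + 3p(1 − p)⁵

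Let p = R × f, where R is the true 3-month risk and f is the share of events visible by day 30. The documents give neither, so both are assumptions shown as a range.

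| R | f = 1 | f = 0.75 | f = 0.5 |
|---|---|---|---|
| 5% | 97% | 98% | 99% |
| 10% | 91% | 94% | 97% |
| 20% | 71% | 81% | 91% |
| 33% | 43% | 61% | 78% |
| 40% | 31% | 49% | 71% |
| 50% | 17% | 35% | 60% |

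Example, R = 40%:
- f = 1, p = 0.40: 0.6³ + 3(0.4)(0.6⁵) = 0.216 + 0.093 = 0.309.
- f = 0.5, p = 0.20: 0.8³ + 3(0.2)(0.8⁵) = 0.512 + 0.197 = 0.709.

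**5. Would a longer wait between cohorts be workable?** At 90 days per cohort, 5 cohorts need at least 450 days (14.8 months) and 10 cohorts need 900 days (29.6 months), before recruitment, treatment or the expansion. The second figure exceeds the expected 24 months. At 30 days the waits are 150 days (4.9 months) and 300 days (9.9 months). This is a reason to keep the day-30 gate and use the later data in another way.

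**The case against.** The strongest reply is that 30 days is a declared choice. The endpoint is called acute toxicity, all sections use 30 days, and later toxicity goes into secondary tables by dose level, where designers of a later trial would see it beside the MTD. That stands: the window is not an error, and later toxicity is not lost. It only has no stated bearing on the dose. The article may also condense a fuller protocol that provides for ongoing safety review. But the article does state the MTD rule and the DLT definitions, and the definitions conflict.

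Several stronger readings are tempting and are not supported:

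- *An event unresolved at day 30 is scored as no DLT.* No section says so. The Study hypothesis wording, "any irreversible grade 4 toxicity during a time frame of 30 days", could mean onset in the window or still unresolved within it. Descriptive Analysis would count the event at once. The release rule permits the next cohort to open but does not compel it.
- *Every patient is followed for 3 months, so two thirds of the toxicity follow-up is ignored.* Death ends follow-up, early patients are followed much longer, and a share of calendar time is not a share of toxicity.
- *The limiting liver toxicity appears after day 30.* The Background describes radiation-induced liver disease without an onset time. Treatment Planning uses late toxicity as an input to the dose calculation, which says nothing about when DLTs occur.
- *The bias is large.* At 5% to 10% risk it is small. The earlier carbon ion escalation study described in the Background, on a 15-fraction schedule, is reported without severe treatment-associated side effects even in the highest dose groups.

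**Conclusion.** The point holds as a cheap improvement to the plan together with a real inconsistency in the DLT definition. As written, the MTD is a 30-day quantity, and no stated rule brings in later related grade 4 toxicity that the trial will have recorded.

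The direction does not depend on the onset assumption: leaving events out can only make escalation more likely, so any bias is upward. The size is unknown. With half of events visible by day 30, the chance of passing a level rises by about 2 percentage points at 5% risk, 6 to 7 at 10%, 35 at 33% and 40 at 40%. These figures rest on assumed risks and an assumed onset share. The point is material only if the 3-month risk is substantial and a real part of it appears after day 30; the documents neither show nor exclude this.

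**What to change.** 1. Reconcile the four DLT definitions (Study hypothesis, Sample Size Calculation, Analysis Variables, Descriptive Analysis) into one. State whether irreversibility and relation to treatment are required, when irreversibility is judged, and how an event unresolved at day 30 is scored for the escalation decision. Which definition is clinically right is for the sponsor to decide.
2. Keep the day-30 gate. Before each later cohort opens, tabulate all related grade 4 events on file at every earlier level.
3. Declare the MTD only after patients at that level have reached the planned 3-month visit or died, and report the 3-month count beside the 30-day count.
4. Pre-specify how the updated count bears on the MTD. This must cover the level expanded to nine patients, because the limit of two or more DLTs in six is not defined for nine.
5. If the sponsor prefers not to use the later data, label the result a 30-day acute-toxicity MTD wherever it is reported.

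Cost: protocol wording plus a decision on item 4. There are no new visits, and the maximum stays at 33. The MTD is declared up to about two months later (90 − 30 = 60 days), within follow-up already planned. A late event may occasionally hold back a cohort.

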### Assessment of Efficacy Parameters

#### - Progression-free Survival and Treatment Response -

Efficacy of the treatment will be recorded according to the RECIST-Criteria (Revised Guidelines, Version 1.1, 2009 [42]):

##### Complete Response (CR)

Disappearance of all target lesions.

##### Partial Response (PR)

at least 30% decrease in the sum of diameters of target lesions, taking a reference the baseline sum diameters.

##### Progressive Disease (PD)

At least a 20% increase in the sum of diameters of target lesions, taking as reference the smallest sum on study (this includes the baseline sum if that is the smallest on study). In addition to the relative increase of 20%, the sum must also demonstrate an absolute increase of a t least 5 mm (Note: The appearance of one or more new lesions is also considered progression).

##### Stable Disease (SD)

Neither sufficient shrinkage to qualify for PR nor sufficient increase to qualify for PD, taking as reference the smallest sum diameters while on study.

The principal investigator or study co-ordinator may be contacted for further discussion on a case by case basis.

### Assessment of Safety Parameters

This study will use the International Common Terminology Criteria for Adverse Events (CTCAE) version 4.0 for toxicity and adverse event reporting. A copy or the CTCAE can be accessed from the CTEP home page: http://ctep.cancer.gov/protocolDevelopment/electronic_applications/ctc.htm

Safety and toxicity of the study treatment will be evaluated by clinical examination, haematological evaluation as well as imaging studies (MRI or CT).

### Statistical calculations for trial sample size

#### Study hypothesis

The study is designed to demonstrate that carbon ion radiotherapy is safe for the treatment of HCC. The aim of the study is to evaluate the optimal dose tolerated with respect to toxicity.

Unacceptable toxicity (DLT) is defined as any irreversible grade 4 toxicity during a time frame of 30 days as classified by CTCAE version 4.0.

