### Statistical Methods

#### Confirmatory Analysis

No confirmatory statistical analysis will be performed. The MTD is determined according to the traditional dose-escalation scheme for Phase I trials in oncology.

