#### Descriptive Analysis

Descriptive summary tables will be presented on baseline patient characteristics as well as for all safety parameters by dose level. Absolute and relative frequencies are reported for all toxicities of the CTC list (NCI CTC-AE Version 4.0) by distinguishing the grading and the assessment of the relation to treatment. Within this study, dose limiting toxicities (DLTs) are defined as any grade IV toxicity according to CTCAE Version 4.0 possibly, probably or definitely associated to study treatment during 30 days after completion of therapy.

A description of the individual load of toxicity of each patient will be made separately using individual descriptions eventually supported by graphical methods.

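### The study hypothesis claims the trial will demonstrate safety, which a rule-based search for an MTD with no confirmatory analysis cannot do

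*Protocol article*

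**What the plan says.** In the protocol article, *Study hypothesis* opens with "The study is designed to demonstrate that carbon ion radiotherapy is safe for the treatment of HCC". The next sentence gives a different purpose: "The aim of the study is to evaluate the optimal dose tolerated with respect to toxicity". *Primary Objective* agrees with the second: "The primary objective is toxicity of carbon ion radiotherapy and the definition of a MTD for subsequent clinical investigation of carbon ion radiotherapy". *Analysis Variables* likewise names the MTD as the primary endpoint.

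The decision rule is in *Sample Size Calculation*. After a clean first cohort: "If none of the three patients shows a DLT, the next cohort of three patients receives the next higher dose as described above". After any DLT in the first three, three more patients are treated at the same dose, and then: "If exactly one out of the six patients (1/6) treated exhibits DLT, the trial continues as planned at the next higher dose level". Two or more DLTs in six stop the escalation, and the level below becomes the MTD and is filled to nine patients.

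On analysis, *Confirmatory Analysis* says "No confirmatory statistical analysis will be performed", and *Descriptive Analysis* says "Absolute and relative frequencies are reported for all toxicities of the CTC list". No section states an acceptable DLT rate, a margin or a bound.

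**The concern.** To demonstrate safety, a trial needs a rate that would count as unsafe and data able to rule that rate out. The article names no such rate and plans no analysis that would exclude one. The opening sentence of the hypothesis therefore gives the design a property it lacks. It also conflicts with the article's own account of the trial as dose finding.

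What is at stake is the conclusion. The MTD is meant for later clinical investigation, and those who plan that work need to know which DLT rates the data leave open. A hypothesis of demonstrated safety, read beside bare proportions from three to nine patients, invites more confidence than the counts can bear.

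**Working it through.** **Inputs from the article.** Cohorts of three; a level is cleared on 0/3 or 1/6; escalation stops on two or more of six; nine patients in total at the MTD; five dose levels. No alpha, power, margin or target DLT rate is stated. The calculation takes DLTs as independent, with one true rate *p* at a given dose. *Study hypothesis* defines the event thus: "Unacceptable toxicity (DLT) is defined as any irreversible grade 4 toxicity during a time frame of 30 days as classified by CTCAE version 4.0". *Descriptive Analysis* words it differently, but the arithmetic is the same for either event.

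**The plan's own figure.** Maximum sample size = 4 × 6 + 9 = 33. This reproduces.

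**Chance that a level is cleared.** A level is cleared by 0/3, or by exactly 1/3 followed by 0/3. Two or three DLTs in the first cohort already make the six-patient count at least two, so they never clear.

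P(cleared) = (1 − p)³ + 3p(1 − p)² × (1 − p)³

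At p = 0.30: 0.343 + (3 × 0.30 × 0.49) × 0.343 = 0.343 + 0.151 = 0.494.

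| True DLT rate | P(cleared) |
|---|---|
| 10% | 90.6% |
| 20% | 70.9% |
| 30% | 49.4% |
| 40% | 30.9% |
| 50% | 17.2% |

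**What the counts exclude.** The exact (Clopper-Pearson) upper limit for x DLTs in n patients is the beta quantile with parameters x + 1 and n − x. For x = 0, the one-sided 95% limit reduces to 1 − 0.05^(1/n). For 0/3 this gives 1 − 0.05^(1/3) = 63.2%, and for 0/9 it gives 1 − 0.05^(1/9) = 28.3%.

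| DLTs/patients | One-sided 95% upper limit | Upper end of two-sided 95% interval |
|---|---|---|
| 0/3 | 63.2% | 70.8% |
| 1/6 | 58.2% | 64.1% |
| 0/9 | 28.3% | 33.6% |
| 1/9 | 42.9% | 48.2% |
| 2/9 | 55.0% | 60.0% |

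The first two rows are the data that allow escalation. The last three are possible results at the MTD.

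**Effect of selecting the dose.** These limits treat the sample as fixed, whereas the MTD is a level that has already passed the clearing rule. At a true rate of 30%, P(0/9) = 0.7⁹ = 4.0%. Every 0/9 result comes from a cleared level, so given clearance the probability is 0.0404 / 0.494 = 8.2%. The 28.3% limit after 0/9 thus does not keep its nominal 5% error at a selected dose, and the data support somewhat less than the table suggests.

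**The case against.** The strongest reply is that this is one loose sentence. The sentence after it, the primary objective and the primary endpoint all describe dose finding. A rule-based Phase I design normally has no margin or target bound, and lacking one is not an error. An interval column in a DLT table is commonly left to the full protocol or the SAP, which are not shown. All of this stands, and it is why the point rests on the stated hypothesis and not on the escalation rule or a missing table.

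A reader might infer that non-detection of DLTs in a handful of patients will be reported as proof of safety. The article does not support that. No section plans such a statement. The planned outputs are an MTD and descriptive tables of all graded toxicities by dose level and relation to treatment, with a description of each patient's toxicity. Safety is therefore not judged on DLTs alone, and the dose carried forward rests on nine patients, not on three or six.

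A reader might also call a dose with a one-in-three DLT rate unacceptable and count its clearance as an error of the design. That benchmark would be an assumption, because the article sets no acceptable rate.

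One thing survives the reply. The agreement of the other sections on dose finding does not repair the hypothesis; it shows that its opening sentence contradicts them.

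**Conclusion.** The point holds, at minor severity. The stated hypothesis conflicts with the primary objective, the primary endpoint and the decision to make no confirmatory analysis, and the design cannot support it. A level with a true 30% DLT rate is cleared about half the time (49%). Even nine patients at the MTD leave rates up to 28% open after 0/9 and up to 43% after 1/9, on one-sided 95% limits that are somewhat optimistic at a selected dose.

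No figure in the article is wrong: the maximum of 33 reproduces, and no escalation decision is affected. The rates in the working are illustrations and not standards taken from the article. The size rests on independent DLTs with a common rate at each dose.

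**What to change.** 1. In *Study hypothesis*, replace the opening sentence with an aim the design can meet, for example: the study will select an MTD by the traditional escalation scheme and estimate the DLT rate and describe toxicity at each dose level; it is not designed to demonstrate safety.
2. In *Descriptive Analysis*, give the exact (Clopper-Pearson) one-sided 95% upper limit beside the DLT proportion at each level and at the MTD. Label these limits descriptive, because they ignore the selection of the dose by the escalation rule.
3. Word any safety statement in terms of that limit, with the same caveat.

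This costs a few sentences and one table column. It needs no further patients or procedures, and the escalation rule and the maximum of 33 stay unchanged. The downside for the sponsor is a less favourable claim: after 0/9, for instance, an upper limit of about 28% in place of a statement that the treatment is safe.

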#### Analysis Variables

Primary endpoint is the MTD chosen between the five dose limits based on the traditional dose escalation scheme. Any unpredictable of irreversible grade 4 toxicity possibly, probably or definitely related the study treatment occurring 30 days after completion of study treatment is considered as dose limiting toxicity.

Secondary endpoints are the collection of safety data on the dose levels used in this trial as well as response, progression-free survival, and overall survival.

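### All four DLT definitions stop at grade 4, so a treatment-related death recorded only as grade 5 is not counted as a DLT and, as written, does not affect escalation

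*Protocol article*

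**What the plan says.** The article defines the DLT in four places:

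- Study hypothesis: "Unacceptable toxicity (DLT) is defined as any irreversible grade 4 toxicity during a time frame of 30 days".
- Sample Size Calculation: "DLT are considered any irreversible Grade 4 toxicity classified by CTCAE version 4.0 after study treatment".
- Analysis Variables: "Any unpredictable of irreversible grade 4 toxicity possibly, probably or definitely related the study treatment occurring 30 days after completion of study treatment".
- Descriptive Analysis: "dose limiting toxicities (DLTs) are defined as any grade IV toxicity according to CTCAE Version 4.0 possibly, probably or definitely associated to study treatment", within 30 days after the end of therapy.

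The grading scale is fixed under Assessment of Safety Parameters: "This study will use the International Common Terminology Criteria for Adverse Events (CTCAE) version 4.0 for toxicity and adverse event reporting".

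The DLT count drives escalation. Under Sample Size Calculation, "If none of the three patients shows a DLT, the next cohort of three patients receives the next higher dose as described above". One or more DLTs among three leads to a second cohort of three at the same level. Exactly one in six lets escalation continue. Two or more in six stops it, and the next lower level becomes the MTD. Analysis Variables makes the MTD the primary endpoint. Interim Analyses plans no look at the data beyond the escalation decisions.

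**The concern.** The four definitions differ on reversibility, on relation to treatment and on the unclear word 'unpredictable'. They agree on one thing: the severity category is a single grade, closed at the top. None mentions grade 5 or death, or uses wording such as 'or higher'. The authors had an open-ended form available, since the Background reports a cited proton study with a 'greater than or equal to' sign before the grade.

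On the adopted scale, death related to an adverse event has its own grade, 5. A related death entered only at that grade falls outside all four definitions, so the most severe toxicity outcome counts as no DLT. The MTD is built from DLT counts alone, so the error runs in one direction: it favours escalation and a higher MTD. That works against the stated aim of showing that the treatment is safe. Reconciling the definitions on reversibility, attribution or window would not remove the gap, because all four share the same upper limit.

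**Working it through.** **The plan's own figure.** The stated maximum of 33 reproduces: four levels of at most 6 patients plus 9 at the MTD, 4 × 6 + 9 = 33. The article gives no DLT rate, death rate, alpha or power, so nothing else can be reproduced.

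**Which events are counted.** Take a related toxicity within the window and compare how it may be recorded:

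| How the fatal case is recorded | Study hypothesis, Sample Size Calculation | Analysis Variables | Descriptive Analysis |
|---|---|---|---|
| Grade 4 event recorded, then death | counts if the grade 4 event is judged irreversible | counts if judged irreversible (or 'unpredictable') | counts |
| Grade 5 only | does not count | does not count | does not count |

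The gap is the second row. That grade 5 means death is a property of the scale the protocol adopts; the article does not spell it out.

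**Effect on one cohort.** Three patients, one grade-5-only related death, no other DLT:

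- As written: 0/3, so the next cohort receives the next higher dose.
- With grade 5 counted: 1/3, so three more patients are treated at the same level.

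**Effect on the chance of passing a level.** With per-patient rate p of counted events, a level is passed on 0/3, or on 1/3 followed by 0/3:

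P(pass) = (1−p)³ + 3p(1−p)² × (1−p)³ = (1−p)³ + 3p(1−p)⁵

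Assumption, not from the document: the true rate of grade 4-5 dose-limiting events is 0.30 per patient. Let f be the part of this, in absolute per-patient terms, that is recorded only as grade 5. The counted rate is then 0.30 − f.

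| f | Counted rate p | (1−p)³ | 3p(1−p)⁵ | P(pass) |
|---|---|---|---|---|
| 0 (all counted) | 0.30 | 0.343 | 0.151 | 0.494 (49%) |
| 0.01 | 0.29 | 0.358 | 0.157 | 0.515 (51%) |
| 0.02 | 0.28 | 0.373 | 0.163 | 0.536 (54%) |
| 0.10 | 0.20 | 0.512 | 0.197 | 0.709 (71%) |

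**How often it would arise.** The chance of at least one grade-5-only death in a cohort of three is 1 − (1−f)³: 3% at f = 0.01, 6% at f = 0.02 and 27% at f = 0.10.

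**After the change.** Counting grade 5 alters only escalation decisions. The maximum remains 4 × 6 + 9 = 33.

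**The case against.** The strongest reply is that many fatal cases would be caught anyway. A patient who passes through a recorded grade 4 event before dying is a DLT under Descriptive Analysis. The same event counts under the other three definitions if judged irreversible, and a toxicity that ends in death is hard to call reversible. This stands, and it limits the point to deaths recorded only as grade 5. A reader might infer that every treatment-related death escapes the DLT count; the text does not support that.

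Second, the article condenses a fuller protocol, where halting rules and safety oversight usually sit. This also stands. A reader might infer that the trial would in practice carry on escalating after a death. The article supports only the narrower statement that the DLT count it defines would not stop it. Investigators would very probably treat such a death as dose limiting. But the definition is stated four times rather than left out, and a primary endpoint should not depend on overriding its own wording. In advanced HCC a death may also come from the disease, so attribution may be disputed, and the written rule then has to settle how the case counts.

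Third, the effect may be small. The cited carbon-ion escalation study of 24 patients is reported as free of severe treatment-associated effects even at its highest doses. That study used 15 fractions rather than four, so the evidence is indirect, but it suggests that the lower rows of assumed death rates are more plausible than 0.10.

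Fourth, a related death would not be hidden. All toxicities are to be tabulated by dose level, grade and relation to treatment, with individual descriptions for each patient. That is true, but those tables do not enter the stated escalation rule.

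**Conclusion.** The point holds in a limited form. As written, a related death within 30 days that is recorded only as grade 5, with no qualifying grade 4 record, is scored as no DLT. One such case among three, with no other DLT, turns a result of 1/3 into 0/3 and sends the next cohort to the higher dose. The article contains no other rule linking a death to the escalation count; whether the full protocol has a safety hold cannot be judged from it.

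The size depends on rates that the document does not give. With an assumed total rate of 0.30, the chance of passing a level moves from 49% to 51% or 54% if the uncounted part is 0.01 or 0.02 per patient, and to 71% only if it is as high as 0.10. The case for correction therefore rests less on the expected numerical effect than on the fact that the primary endpoint's definition omits the highest grade of its own scale, and that the error favours escalation. No figure in the article is wrong because of it.

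**What to change.** Reconcile Study hypothesis, Sample Size Calculation, Analysis Variables and Descriptive Analysis into one DLT definition, stated once and referred to elsewhere. Make its severity category open at the top (grade 4 or higher), so that grade 5 events meeting the agreed window and attribution conditions enter the escalation count and the MTD. State that any reversibility condition does not apply to grade 5. This belongs in the same edit that settles the four passages' other differences.

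The cost is a few words in four places. No further data are needed, because deaths are already followed for overall survival and all toxicities are already graded. The escalation thresholds and the maximum of 33 patients do not change. The downside is that escalation may stop earlier if a related death occurs.
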